### Dietary intervention

The patients of the intervention group received oligofructose-enriched inulin (Orafti® Synergy 1, Beneo, Tienen, Belgium) for 3 months, whereas children of the placebo group received maltodextrin (Maltodextrin DE 20, Hotrimex, Konin, Poland) during the same period. Synergy 1 (DP3–9: 50% ±10, DP ≥ 10: 50% ±10, according to the producer) is the commercially available preparation of chicory inulin enriched by a specific fraction of oligofructose produced by partial enzymatic hydrolysis of chicory inulin. Both supplements, Synergy 1 and maltodextrin, were similarly light yellow powders of slightly sweet taste. Both substances are approved food grade ingredients, and they have been previously used in other clinical trials [18, 19]. Synergy 1 and maltodextrin were packed in identical white disposable sachets by the outsourcing company (DorTech, Pobiedziska, Poland). During the enrolment visit (T0), each participant was provided with a package of sachets containing the appropriate supplement in the amount required for a 3-month intervention. The participants from the experimental group received sachets containing 10 g of oligofructose-enriched inulin, whereas the participants from the placebo group received packages containing 7 g of maltodextrin. The packages with the appropriate supplement were distributed by a researcher who was familiar with the identity of the groups. The participants were instructed to consume the contents of one sachet daily for 3 months while closely following a GFD. The medium for suspending the supplement (water, juice or yoghurt) was chosen by the participants and could be changed during the trial. The participants were also provided with a questionnaire of compliance and adverse reaction, and were asked to record their daily intake of the supplement, any adverse reactions (gastrointestinal and other) and any other drugs taken during the trial. The participants who did not consume the supplement for more than 80% of the trial period were eliminated from the study. Before the end of the intervention, all participants were asked to complete a brief questionnaire assessing their mental wellbeing and stool characteristic (frequency and consistency). In the questionnaire, they were asked to provide information based on the observations made in the last week of the supplement intake. The participants were also asked to complete a Food Frequency Questionnaire with 6 answers (FFQ-6). At the end of the 12-week intervention, the participants were asked to return any remaining sachets of the Synergy 1 supplement or the placebo for assessment of the compliance.

### Data collection

Data were collected during the enrolment visit (T0), a visit at the end of the intervention (T1) and regular follow-up visits that took place every 3 months in the Gastroenterology Clinic. Demographic data were collected during the T0 visit. Anthropometric data and biological samples (blood, urine and faeces) were collected during T0 and T1 visits. The participants were provided with sterile containers for collecting urine and stool samples. An assessment of GFD compliance during the trial was performed at the end of the study.

### Anthropometric indices

Information about the participants’ body weight, height and nutritional status was collected by a nurse with the use of standard methods. The participants were weighed in light clothing and without shoes on a professional scale (Seca, Hamburg, Germany) with a weight limit of 200 kg and accuracy of 0.1 kg. Body height was measured on a standard stadiometer (Seca, Hamburg, Germany). The body mass index (BMI) was calculated as body mass divided by the square of body height, and it was expressed in kg/m^2^ and in standard deviation scores (SDS) based on age- and sex specific reference values. Detailed information relating to the measured anthropometric parameters is presented in Table 2.

**Table 2 Tab2:** The participants’ baseline anthropometric data

	Total sample		Intervention group		Placebo group	
N	34		18		16	
Gender						
Girls	21 (61.8%)		11		10	
Boys	13 (38.2)		7		6	
	Range	Av^a^	Range	Av	Range	Av
Age (years)	4–17	10	5–17	10	4–16	10
Weight (kg)	15.0–78.0	35.3	15.0–67.9	36.6	16.3–66.8	33.7
Height (cm)	103–183	138.8	110–183	140.6	103.0–172.0	136.8
*BMI (kg/m* ^*2*^ *)*	12.5–28.4	17.1	13.5–23.3	17.2	13.7–28.4	17.0

^a^Average

### Diet control

In line with STROBE-nut recommendation [16], in the present study a modified FFQ-6 was applied [20]. It is a semi-qualitative food intake frequency questionnaire commonly used as a retrospective dietary assessment method suitable to evaluate the relation between consumed food and disease [21]. The applied FFQ-6 was a modified version from the original FFQ-6 (available online [20]) that was developed and validated using a reliability testing method in the population of young women (aging form 13–21 years old) from Olsztyn, Poland. The reliability of FFQ-6 was assessed by comparison of the results of first interview (test) with results obtained for the same group of respondents under the same conditions after 2 weeks (retest) [22]. The Spearman correlation coefficient and Cohen’s *kappa* coefficient tests were used to assess the reliability of the questionnaire FFQ-6 (test-retest). High Spearman correlation coefficient (ranged from 0.5 to 0.7) was determined for 42% of total food products, while very high correlation coefficient (0.7–0.9) was obtained for 50% of products. Cohen’s *kappa* coefficient ranged from 0.32 to 0.72. High test-retest reliability (*kappa* = 0.6–0.8) was obtained for 16% of total food products, while moderate reliability (*kappa* = 0.4–0.6) was obtained for 81% of products.

For the dietary assessment of a GFD compliance by CD children participating in the present study, we modified the original FFQ-6 by adding additional gluten-free items into the cereal products section [see Additional file 1], whereas other sections remain unchanged. At the moment the validation of modified FFQ-6 (by retest in 50% of study participants; 2-weeks after the test) studies take place. Modified FFQ-6 was distributed by mail to all study participants before T1 visit together with detailed instructions on how to complete it. The parents or caregivers were asked to fill in a questionnaire relating to the frequency with which different foods were consumed by the children during the entire trial (3-months intervention). The applied FFQ-6 reported the frequency of consumption of 63 food products representing eight groups: sweets and snacks; dairy products and eggs; cereal products; fats; fruits; vegetables; meat and fish products; beverages. The portion sizes were not considered. Consumption frequency was ranked on the following grading scale: never or almost never (1 point), once a month or less frequently (2 points), several times per month (3 points), several times per week (4 points), every day (5 points) and several times per day (6 points).

Moreover, to assess a compliance to a GFD, a serum anti-tissue transglutaminase (tTG) antibodies and faecal gluten immunogenic peptides (GIP) concentration will be analysed, whereas the balance of selected nutrients, in particular of vitamins and amino acids, will be analysed in plasma and urine of CD children at T0 and T1 visits.

### Sample collection

A fasting blood test was conducted in the morning, and blood samples were collected by a qualified nurse in the hospital laboratory. Three vials of blood were collected from every participant: 1) 1.6 mL into a vacuum tube containing EDTA for hematologic analysis; 2) 5 mL into a vacuum tube for biochemical serum analyses; 3) 5.5 mL into a vacuum tube containing an anticoagulant (heparin) for plasma analyses. Blood samples from vials 1 and 2 were processed according to standard procedures in the hospital laboratory. Blood samples from vial 3 were transported on ice, centrifuged at 3500 rpm for 10 min, and plasma aliquots (100 μL) were stored at −80 °C.

Not later than 3 days before the visit, faecal samples were collected, frozen and transported on ice to the clinic. On the day of the visit at the clinic, a fresh urine sample (second spontaneous urine) was collected in the morning (before breakfast). The samples provided by the participants were immediately separated into aliquots of approximately 1 mL (urine) and 100 mg (faeces) each and were stored at −80 °C until further analysis.

### Analysis of morphological and biochemical blood parameters

The complete blood count, blood biochemical parameters (creatinine, aspartate aminotransferase - AST, alanine aminotransferase - ALT, C-reactive protein – CRP, albumin, protein, calcium, phosphorus, magnesium, sodium, potassium, chloride, ferritin), tTG and urine biochemistry parameters (creatinine, calcium, phosphorus, magnesium, sodium, potassium) were analysed according to standard procedures in the Hospital’s Department of Laboratory Diagnostics and Transfusion Serology. The content of fat-soluble vitamins in plasma will be determined by a chromatographic method (HPLC-DAD for vitamins A and E) or in the enzyme-linked immunosorbent assay (ELISA) for vitamin D, using commercial kits. The content of water-soluble vitamins (B1, B2, B6, B9, B12) in plasma will be assayed using the HPLC-DAD method. The profile of amino acids in plasma will be analysed via EZ:Faast™ derivatisation method followed by gas chromatography/mass spectrometry detection (GC-MS). All parameters will be analysed at the beginning and at the end of the study.

### Urine analysis

Selected urine biochemical parameters (creatinine, calcium, phosphorus, magnesium, sodium, potassium) were analysed according to the standardized procedures in the diagnostic laboratory of the Children’s Hospital in Olsztyn. The analysis of amino acid profile in urine will be performed by the method described above (section: Analysis of morphological and biochemical blood parameters). All urine parameters were analysed both at T0 and T1 visits.

### Gut microbiota characteristics, short-chain fatty acids and GIP concentration

Bacterial genomic DNA will be isolated from faecal samples with the use of a dedicated commercial kit (GeneMATRIX Stool DNA Purification Kit, EURx, Gdańsk, Poland) for a quantitative analysis of gut microbiota. The quantitative characteristics of intestinal bacteria will be determined using the Real-Time PCR technique and group-specific primers. The DNA of strains representing the predominant bacterial groups will be the positive control, and it will be used to develop the standard curve. The total counts of *Bifidobacterium, Bacteroides*-*Prevotella*-*Porphyromonas, Clostridium coccoides, C. leptum* and *Lactobacillus* communities will be determined.

The concentration and profile of short-chain fatty acids (SCFAs), which are indicative of the activity of gut microbiota, will be determined in the faecal samples of all participants by gas chromatography with a flame ionization detector (GS-FID).

A quantity of GIP in faecal samples will be determined using a commercial Sandwich ELISA kit (Biomedal Diagnostics, Sevilla, Spain). Gut microbiota profiles, SCFAs and GIP concentration analysis will be performed in the faecal samples collected at T0 and T1 visits.

### Sample size

To our knowledge, this study makes the first attempt to evaluate the effects of fructan supplementation on children with CD, therefore, it was performed as a pilot trial without calculating sample size. Our plan was to recruit approximately 30 children (15 subjects per arm) with diagnosed CD on the assumption that the drop-out rate would reach approximately 20% (12 participants in each arm would complete the trial). The results obtained in the pilot study will be used to calculate the sample size for a fully-powered study that will be carried out in the future on paediatric CD patients receiving oligofructose-enriched inulin with GFD.

### Statistical analysis

Anthropometric and demographic data will be analysed using descriptive statistical methods. The participants whose reported intake of the Synergy 1 supplement or the placebo exceeded 80% of the prescribed intake will be included in final analyses. Statistical analyses will be performed in duplicate and expressed as mean values and standard deviation (SD). The influence of prebiotic supplemented-GFD and placebo supplemented –GFD on the measured parameters will be determined by one-way analysis of variance (ANOVA). If the differences between experimental and placebo groups are statistically significant (*P* < 0.05), the data will be subjected to post-hoc comparisons with the use of Fisher’s Least Significant Difference (LSD) test. The side effects of supplementation will be expressed by the percentage of each effect noted in the experimental group or the placebo group. The average consumption of food products by CD children during the intervention trial obtained from FFQ-6 will be compared in the Kruskal-Wallis test. Data will be processed statistically using Statistica 12 software (StatSoft, USA).

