### Research objective and hypothesis

We hypothesized that adherence to a GFD supplemented with oligofructose-enriched inulin would deliver health benefits to children suffering from CD without any side effects, and that it would alleviate intestinal inflammation, restore and stabilize balance of a gut microbiota and reverse nutritional deficiencies through enhanced absorption of vitamins and minerals. The main aim of this clinical trial is to evaluate the impact of an oligofructose-enriched inulin (Synergy 1) on selected biochemical parameters and nutritional status of paediatric CD patients following a GFD. Attempts are also being made to determine the influence of the oligofructose-enriched inulin supplement on the quantitative composition and the activity of intestinal microbiota.

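### Anthropometry, one component of the nutritional status in the main aim, is assigned to description with demographics, so no baseline-adjusted between-arm estimate of it is planned

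*Protocol article*

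**What the plan says.** All references are to the protocol article.

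- **Research objective and hypothesis.** The main aim is the impact of the supplement "on selected biochemical parameters and nutritional status of paediatric CD patients following a GFD". The hypothesis for the nutritional effect is that the supplement would "reverse nutritional deficiencies through enhanced absorption of vitamins and minerals". No hypothesis about growth or BMI is stated.
- **Data collection.** "Anthropometric data and biological samples (blood, urine and faeces) were collected during T0 and T1 visits". Anthropometry is therefore a before-and-after measurement, not only a baseline descriptor.
- **Anthropometric indices.** Under this heading a nurse records nutritional status along with weight and height. BMI is "expressed in kg/m^2^ and in standard deviation scores (SDS) based on age- and sex specific reference values". The section adds: "Detailed information relating to the measured anthropometric parameters is presented in Table 2". Table 2 holds baseline values.
- **Statistical analysis.** "Anthropometric and demographic data will be analysed using descriptive statistical methods". A later sentence says that the influence of the two supplemented diets "on the measured parameters will be determined by one-way analysis of variance (ANOVA". Side effects are given as percentages, and the food frequency data go to a Kruskal-Wallis test.

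**The concern.** The analysis section assigns methods by class of data, and the only method named specifically for anthropometry is description, in the same sentence as demographics. That suits a baseline table. It does not suit a variable that is measured again after 12 weeks and belongs to a domain named in the main aim. Followed as written, the trial reports weight, height and BMI by arm but gives neither a treatment difference nor an interval for any of them.

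The stake is modest but real. The Sample size section says that the pilot results will be used to size a full trial. Arm-wise means and SDs serve that purpose less well than a baseline-adjusted difference with its interval and residual SD.

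**Working it through.** **Step 1: is anthropometry part of the aim?** The aim lists nutritional status beside biochemical parameters, and the Anthropometric indices section places nutritional status under its own heading. Anthropometry is therefore one component. It is not the whole: vitamins, amino acids, minerals, ferritin, albumin and protein are measured at the start and the end, and the stated hypothesis concerns them.

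**Step 2: which analysis does each component get?**

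| Component | Measured | Method named |
|---|---|---|
| Biochemical nutritional markers | T0 and T1 | Between-arm one-way ANOVA |
| Weight, height, BMI, BMI SDS | T0 and T1 | Descriptive statistics |

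The word *only* is not in the text. The ANOVA sentence speaks of measured parameters, and the Anthropometric indices section uses the same term for anthropometry, so two readings are possible:

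- Reading A (plain): anthropometry is described, and no between-arm estimate is planned.
- Reading B: the descriptive sentence covers the baseline table, and the ANOVA covers the outcome. A one-way model has the arm as its single factor and no term for the T0 value.

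**Step 3: does T0 matter here?** Table 2 gives ages 4–17 overall and these baseline means (intervention vs placebo):

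- weight: 36.6 − 33.7 = 2.9 kg
- height: 140.6 − 136.8 = 3.8 cm
- BMI: 17.2 − 17.0 = 0.2 kg/m²

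The weight and height gaps existed before any supplement was taken and would carry into an unadjusted T1 comparison. The BMI gap is small. BMI SDS by arm is not tabulated.

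**Step 4: precision without adjustment.** The article gives no outcome SD, so the unit is one SD of the T1 value. The 95% half-width is t(0.975, n1+n2−2) × √(1/n1 + 1/n2).

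- The plan's own figure first: 12/(1 − 0.20) = 15 recruited per arm, which reproduces the Sample size section.
- Expected completers, 12 vs 12: 0.85 SD.
- Randomised, 18 vs 16: 0.70 SD.

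**Step 5: gain from adjusting for T0.** Let ρ be the T0–T1 correlation. The documents do not give it; 0.8 to 0.95 is assumed. The standard error multiplier relative to an unadjusted T1 comparison is √(1 − ρ²).

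| ρ | Multiplier | Half-width, 12 vs 12 | Half-width, 18 vs 16 |
|---|---|---|---|
| 0.80 | 0.60 | 0.85 × 0.60 = 0.51 SD | 0.70 × 0.60 = 0.42 SD |
| 0.90 | 0.44 | 0.85 × 0.44 = 0.37 SD | 0.70 × 0.44 = 0.31 SD |
| 0.95 | 0.31 | 0.85 × 0.31 = 0.26 SD | 0.70 × 0.31 = 0.22 SD |

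These half-widths ignore the one degree of freedom spent on the covariate, which changes them little.

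**The case against.** **The nutritional aim does get a between-arm answer.** A reader might infer that the whole nutritional-status part of the aim goes unanswered. The documents do not support that. The hypothesised effect runs through vitamins and minerals, and those markers fall under the ANOVA. This objection stands, and the point is confined to the anthropometric component.

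**The text does not forbid a comparison.** Pairing anthropometry with demographics fits a baseline-characteristics sentence, and the ANOVA sentence excludes nothing. This stands in part: Reading A is the natural one, because the section assigns a method to each class of data, but it is an inference. If Reading B is intended, the section should say so, and the missing T0 term remains.

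**The ANOVA might be run on changes.** The article does not say whether T1 values or changes are analysed. With equal SDs at the two visits, a change score has multiplier √(2(1 − ρ)), which is 0.63 at ρ = 0.8 and 0.32 at ρ = 0.95, close to ANCOVA's 0.60 and 0.31. The gain in Step 5 is therefore a gain over an analysis of T1 alone.

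**Normal growth will not pass unnoticed.** A reader might infer that description invites normal growth to be taken for benefit. The concurrent placebo arm, the randomisation stratified by sex and age, and BMI expressed "in standard deviation scores (SDS) based on age- and sex specific reference values" largely answer that. The article gives no figure for growth over 12 weeks.

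**Description is acceptable in a pilot of 34.** With no sample size calculation, a test would have little power. That is fair against a test, but an estimate with a wide interval makes no claim to power, and the plan already tests other outcomes at P < 0.05.

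**Conclusion.** The point holds in a limited form. Anthropometry is measured twice and is one component of the nutritional status in the main aim, yet the only method named specifically for it is descriptive. On the plain reading it gets no between-arm estimate. On the alternative reading it gets a one-way ANOVA with no T0 term.

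The multipliers of 0.60 to 0.31 measure what baseline adjustment would gain over an unadjusted T1 comparison. They do not measure harm done by description, and they rest on the assumed correlation of 0.8 to 0.95. Even the adjusted interval, about 0.2 to 0.5 SD either side, remains a pilot estimate.

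This is an inexpensive improvement to the analysis section. It does not show that the main aim goes unanswered.

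**What to change.** In the Statistical analysis section:

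1. Limit the descriptive sentence to demographics and the T0 table.
2. Add that the between-arm difference in T1 BMI SDS will be estimated by ANCOVA with the T0 value as covariate and reported with a 95% CI, labelled as an exploratory pilot estimate.
3. Treat height SDS in the same way if it is derived from height, age and sex. The article mentions SDS for BMI only.
4. Report raw weight descriptively and do not use it for inference.

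If the authors regard anthropometry as outside the nutritional-status aim, one sentence saying so would also settle the ambiguity.

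The cost is one or two sentences. The T0 and T1 measurements are already part of the trial, so no further visits or data are needed.

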### Randomization and blinding

Patients have been randomly assigned to an intervention group (*n* = 18) or a placebo group (*n* = 16). Stratified randomization based on gender and age was conducted by a researcher not directly involved in the study. Separate randomization procedures were carried out for boys and for girls to produce comparable groups. The trial had a design where the researchers, laboratory personnel (excluding the researcher who distributed the supplement or the placebo to the participants) and the participants were not aware which subjects were receiving the supplement and which were receiving the placebo.

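### The only stated analysis set is children reporting more than 80% intake, a post-randomisation selection that may bias the comparison by an unknown amount in an unknown direction

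*Protocol article*

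**What the plan says.** The rule appears in two places in the protocol article.

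- **Statistical analysis:** the final analyses take in children, in either arm, whose reported intake "exceeded 80% of the prescribed intake will be included in final analyses". The effect of the two supplemented diets "on the measured parameters will be determined by one-way analysis of variance (ANOVA"), with significance at P < 0.05. Side effects are to be given as percentages per group, with no denominator stated.
- **Dietary intervention:** "The participants who did not consume the supplement for more than 80% of the trial period were eliminated from the study". Families recorded daily intake and adverse reactions on the same questionnaire. At the end they were "asked to return any remaining sachets of the Synergy 1 supplement or the placebo for assessment of the compliance".

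Randomization and blinding gives 18 children on the supplement and 16 on placebo. Sample size contains the only attrition figure: it assumes that "the drop-out rate would reach approximately 20% (12 participants in each arm would complete the trial"), starting from 15 per arm. That figure is called drop-out and is not tied to the 80% rule. The same section says that the pilot results will be used to calculate the sample size of a full trial. The stated hypothesis is benefit free of side effects. No all-randomised analysis is mentioned, even as a sensitivity analysis.

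**The concern.** Randomisation makes the 18 and the 16 comparable. It does not make comparable the subsets that go on to report more than 80% intake. Intake is measured after allocation, and the arms take different substances (10 g of oligofructose-enriched inulin against 7 g of maltodextrin), so the product itself may influence who passes the cut. The study also measures stool characteristics, faecal bacteria, short-chain fatty acids and nutritional markers, so reasons for low intake could be related to outcome.

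Three results are exposed:

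- the between-group test at P < 0.05;
- the side-effect percentages, which bear directly on the hypothesis and would lose any child whose symptoms led to low intake;
- the effect and variance estimates carried into the sample size of the full trial, which would describe adherers only.

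This does not rest on something an unseen analysis plan might supply. The article itself fixes the population for the final analyses. If removal also meant that no end-of-intervention (T1) sample was taken, no later plan could restore those data.

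**Working it through.** **1. The plan's own figure.** 15 × (1 − 0.20) = 12 completers per arm, as stated. Applied to the numbers randomised, the same 20% leaves 18 × 0.8 = 14.4 and 16 × 0.8 = 12.8, together 27.2 of 34. About 7 children would be left out. Using 20% for adherence exclusions is an assumption, since the article gives it for drop-out only.

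**2. Precision.** The standard error of a mean difference, in SD units, is √(1/n₁ + 1/n₂).

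- All randomised: √(1/18 + 1/16) = 0.344.
- After about 20% loss: √(1/14 + 1/13) = 0.385.

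**3. Possible bias with no true effect.** Suppose the outcome correlates r with the tendency to adhere, and the k lowest of n on that tendency are excluded. The retained mean then shifts by r × m(n,k) SD, where m(n,k) is the expected mean of the n − k largest of n standard normal values. By simulation, m(18,4) = 0.364, m(16,3) = 0.311 and m(16,2) = 0.219. The values of r (0.3, 0.5, 0.7) and the exclusion counts are assumptions; the article gives none by arm.

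| Exclusions (active / placebo) | Shift | r = 0.3 | r = 0.5 | r = 0.7 | False-positive rate |
|---|---|---|---|---|---|
| 4/18 and 3/16, same mechanism | r × (0.364 − 0.311) | 0.02 | 0.03 | 0.04 | about 5%, 6%, 7% |
| 4/18 and 2/16, same mechanism | r × (0.364 − 0.219) | 0.04 | 0.07 | 0.10 | about 5%, 6%, 7.5% |
| 4/18 selective, 2/16 at random | r × 0.364 | 0.11 | 0.18 | 0.25 | about 6%, 8%, 11% |

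The rates come from simulated two-group tests at two-sided 0.05 (the article does not state sidedness). In the first row the small excess over 5% comes mainly from removing a fixed number of the lowest-ranked children. This shrinks the within-arm spread and makes the standard error too small; the mean shift itself adds little.

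**4. Cross-check with the large-sample formula.** The shift for an excluded fraction q is r·φ(z_q)/(1 − q), and the factor is 0.350 at q = 0.20. Exclusion of 20% in both arms by the same mechanism gives exactly 0. Exclusion of 20% against none gives 0.105 to 0.245 SD. A more extreme 40% against none gives 0.19 to 0.45 SD.

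**5. Side effects (invented counts).** If 4 of 18 supplemented children fall below the cut because of a symptom and 3 of the other 14 also report it, the rate is 3/14 = 21% among adherers and (4 + 3)/18 = 39% among all randomised.

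**6. The two statements of the rule.** Statistical analysis uses the reported share of prescribed intake. Dietary intervention uses the share of the trial period, and its wording could also be read as removing only children who missed more than 80% of it. Returned sachets serve as a compliance check, but the article does not say whether they override the reports.

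**The case against.** The rule is stated in advance, is the same in both arms, and belongs to a pilot with no power calculation. The only attrition assumption is equal in the two arms, and under near-equal exclusion by one mechanism the bias is close to nothing. That stands, and it limits the claim to a risk.

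A reader might infer more, and the documents do not support it:

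- **That the bias favours the supplement.** This needs exclusion that differs between arms and a link between adherence and outcome in the favourable direction. The article establishes neither, and for many of the vitamins, amino acids, minerals and bacterial counts it does not say which direction is favourable.
- **That the analysed children are those who tolerated the powder, and that placebo children have no comparable reason to stop.** The rule selects on reported intake, which taste, forgetting or illness can also lower. Both arms record reactions, and the Background notes that symptoms continue in many patients on a gluten-free diet.
- **That 12 weeks and 3 months create rival thresholds.** The article uses the two interchangeably, and with one sachet a day the share of period and the share of intake are nearly the same quantity. This is operational detail. Only the ambiguous wording needs reconciling.

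The timing objection also stands. Recruitment ran from November 2015 to January 2016, the intervention lasted 12 weeks, and the article appeared in August 2017 with the conduct in the past tense. Missed T1 samples cannot now be collected. The statistical analysis is still described as future, so the analysis set can be changed.

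Pilot status does not remove the point. The stated aim is a between-group effect tested for significance, and an adherence-defined set is acceptable beside an all-randomised analysis but not as the only one.

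**Conclusion.** The concern holds as a defect in the stated analysis set. As written, the final analyses compare subsets chosen on post-randomisation behaviour, with no all-randomised comparison beside them. The size and direction of any bias cannot be derived from the article. Under assumed correlations of 0.3 to 0.7, it runs from about 0.02 to 0.04 SD (near-equal exclusion, same mechanism) to about 0.11 to 0.25 SD (4 of 18 selectively on active, 2 of 16 at random on placebo). The upper range describes one unfavourable scenario and should not be read as an estimate. For scale, the standard error with all 34 children is 0.344 SD. The side-effect percentages are exposed in the same way if low-intake children are left out of the denominator.

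**What to change.** - Make the main analysis all randomised children with available T1 data, in their allocated arm and whatever their intake.
- Report side effects on all children who received product, and state that denominator.
- Report the number excluded, and the reasons, for each arm.
- Keep the over-80% set as a labelled secondary analysis with one definition, reconciling Dietary intervention with Statistical analysis and naming the data source (reported intake or returned sachets).
- Use the all-randomised estimates when sizing the later trial.

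The cost is mainly wording and a few extra tabulations. The estimated effect may be slightly smaller when low-intake children are included. Any child removed without T1 samples is lost to the main analysis; the number per arm should be given and stated as a limitation.

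### ANOVA with mean and SD is the only method named for laboratory outcomes; applied untransformed to skewed assays, it could lose much of the power and yield poor planning figures for the next trial

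*Protocol article*

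**What the plan says.** The Statistical analysis section sets one rule for laboratory data. Results are "expressed as mean values and standard deviation (SD"), and the effect of supplement against placebo "on the measured parameters will be determined by one-way analysis of variance (ANOVA"), with P < 0.05 as the threshold and Fisher's LSD as follow-up. The only rank-based method is for food consumption, where the averages "obtained from FFQ-6 will be compared in the Kruskal-Wallis test".

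The parameters this rule covers are listed elsewhere. The section on blood parameters includes CRP, ferritin and tTG. The section on gut microbiota says "The quantitative characteristics of intestinal bacteria will be determined using the Real-Time PCR technique and group-specific primers", with a standard curve giving total counts for five bacterial groups; it adds SCFA concentrations and says "A quantity of GIP in faecal samples will be determined using a commercial Sandwich ELISA kit". The Diet control section uses tTG and GIP to judge adherence to the gluten-free diet.

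No section names a scale, a transformation, a distribution check, or a rule for values below an assay limit. The Sample size section says that the pilot's results will be used to size a fully powered trial.

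**The concern.** Counts read from a qPCR standard curve can differ between children by large factors, and CRP and ferritin are typically right-skewed. With 12 to 18 children per arm, one or two high values can dominate a mean and an SD, and a real proportional change in bifidobacteria can be lost in the spread. tTG and GIP may have many values at the assay floor, where a mean depends on what is substituted for the undetectable results.

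Two things are at stake. One is the chance of seeing a real effect on the skewed outcomes. The other is the quality of the means and SDs that the full trial will be planned on.

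**Working it through.** **Inputs from the article.** 18 and 16 children randomized; 15 per arm planned; 20% drop-out; 12 completers per arm; P < 0.05. No effect size, SD, skewness, assay limit or power is stated.

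**The plan's own figure.** 12 / (1 − 0.20) = 15 per arm, which reproduces. It is a recruitment figure, not a power calculation.

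**Assumptions.** Values are lognormal and the effect is multiplicative, which is the setting that suits a log analysis. With two groups, the ANOVA F test gives the same p-value as the pooled two-sided t test. Trials were simulated, at least 20,000 per setting, and analysed on the log and raw scales without baseline adjustment.

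**Power for a true rise of 0.5 log10 (about 3.2-fold), log scale vs raw scale:**

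| Between-child SD (log10) | 12 vs 12 | 18 vs 16 |
|---|---|---|
| 0.4 | 83% vs 65% | 94% vs 79% |
| 0.6 | 50% vs 24% | 65% vs 32% |
| 0.8 | 31% vs about 10% | 42% vs 12% |

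Exact noncentral-t power with 12 per arm confirms the log-scale column: 83%, 50% and 31%.

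**How the loss depends on skew.** Take an effect of one SD on the log scale and 12 per arm. Log-scale power is 65% throughout, and a rank test has 60 to 61%. Raw-scale power falls as the SD of the natural-log values rises: 63% at 0.25, 60% at 0.5, 44% at 1.0, 29% at 1.5 and 14% at 2.3. The loss is about 2 to 5 points at low skew and about 20 or more from 1.0 upward.

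**Type I error.** Raw-scale ANOVA becomes conservative: 3.4 to 3.8% at an SD of ln values of 1.0, and 1.3 to 1.4% at 2.3.

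**Planning the next trial.** Take 80% power and two-sided 5%, so (1.96 + 0.84)² ≈ 7.85, and the same 0.5 log10 rise.
- Log scale: n per arm = 2 × 7.85 × (SD / 0.5)². This gives 10.0, 22.6 and 40.2, so 11, 23 and 41.
- Raw scale: with ratio r = 10^0.5 = 3.16 and a common coefficient of variation CV, n per arm = 7.85 × CV² × (1 + r²) / (r − 1)² ≈ 18.5 × CV². For a lognormal, CV² = exp(s²) − 1 with s = 2.303 × SD. CV² is 1.34, 5.74 and 28.8, so n is about 25, 107 and 530.

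At SD 0.6 log10 the raw SD is √5.74 ≈ 2.4 times the mean. These raw-scale figures use population values; estimates from 12 to 18 children would be unstable as well.

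**Assay floor.** Assume an SD of ln values of 1.0 and a true mean of 1.65. With half the values below the limit, the mean is 1.38, 1.63 or 1.89 when 0, half the limit or the limit is substituted. With 90% below, it is 0.64, 2.26 or 3.88.

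**The case against.** The strongest reply is that the article never mentions untransformed values. ANOVA of log10 counts, with mean and SD of log10 counts, would fit its wording. A transformation or a detection-limit rule could sit in an analysis plan that is not shown, and an article is not at fault for leaving such detail to it. The sentence on mean and SD also speaks oddly of statistical analyses done in duplicate, so it may partly describe assay replicates. This stands to the extent that a reader might infer a commitment to the raw scale, and the text does not support that. What answers the rest is that the section does not defer the method. It states the summary, test, threshold, post-hoc test and software, and it names a rank test but gives it to one questionnaire only. Followed literally, it applies ANOVA to total counts and concentrations. Read generously, it leaves the scale open until the data are seen.

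Other stronger readings also go too far:
- **All laboratory outcomes are harmed.** Sodium, potassium, chloride, albumin and similar analytes are probably near-symmetric, and there the loss is small.
- **False positives are a risk.** The error rate falls rather than rises.
- **Most tTG and GIP values will be undetectable.** At least 6 months of gluten-free diet makes this plausible, but the article gives no assay limit or share, and its Background cites compliance from 80% down to below 40%. These are adherence markers, so for them description matters more than power.
- **The microbiota effect is the main aim.** The stated main aim is biochemical parameters and nutritional status; microbiota follows as a further attempt.
- **A promised power is undermined.** The trial is a pilot with no stated power.

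**Conclusion.** The point holds in limited form. ANOVA with mean and SD is the only method named for all measured parameters, and nothing is provided for assays likely to be strongly skewed or censored. If it is applied to untransformed values, the loss for the skewed assays is substantial: roughly 18 to 26 percentage points with 12 per arm across the assumed SDs of 0.4 to 0.8 log10. The resulting means and SDs could overstate the next trial's sample size by a factor of about 2 to 13 (25/11 to 530/41). There is no inflation of type I error and little effect on near-symmetric analytes.

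These sizes rest on lognormal data, a 0.5 log10 effect and SDs that the article does not supply. The assay-floor point is conditional on many values being undetectable. This is a change worth making, not a flaw that invalidates the trial.

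**What to change.** State that qPCR counts (log10), CRP, ferritin and, if skewed, SCFAs at T1 are analysed by ANCOVA with the log T0 value as covariate. Report geometric mean ratios with 95% confidence intervals, and the log-scale SD for planning the full trial. Say how values below the quantifiable range enter the log analysis. If many tTG and GIP values fall below the assay limit, compare them by ranks and report the share detectable with median and quartiles. Ranks keep more information than a simple detectable/undetectable split in arms this small. Near-symmetric analytes can keep mean and SD.

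The cost is a few sentences and no new data, since T0 and T1 samples are already part of the design. The downside is that effects on the logged outcomes are read as ratios, not differences. The choice should be recorded before outcomes are compared by arm.
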